## Abstract

**Background:**

Chest complaints presented to a general practitioner (GP) are frequently caused by diseases which have advantageous outcomes. However, in some cases, acute coronary syndrome (ACS) is present (1.5-22% of cases). The patient’s signs, symptoms and electrocardiography results are insufficient diagnostic tools to distinguish mild disease from ACS. Therefore, most patients presenting chest complaints are referred to secondary care facilities where ACS is then ruled out in a majority of patients (78%). Recently, a point of care test for heart-type fatty acid-binding protein (H-FABP) using a low cut-off value between positive and negative of 4 ng/ml has become available. We aim to study the role of this point of care device in triage of patients presenting chest complaints possibly due to ACS, in primary care. Our research protocol is presented in this article. Results are expected in 2015.

**Methods/Design:**

Participating GPs will register signs and symptoms in all patients presenting chest complaints possibly due to ACS. Point of care H-FABP testing will also be performed. Our study will be a derivation study to identify signs and symptoms that, combined with point of care H-FABP testing, can be part of an algorithm to either confirm or rule out ACS. The diagnostic value for ACS of this algorithm in general practice will be determined.

**Discussion:**

A safe diagnostic elimination of ACS by application of the algorithm can be of significant clinical relevance. Improved triage and thus reduction of the number of patients with chest complaints without underlying ACS, that are referred to secondary care facilities, could lead to a substantial cost reduction.

**Trial registration:**

ClinicalTrials.gov, NCT01826994, accepted April 8^th^ 2013.

## Background

### Daily practice

Patients presenting with chest complaints caused by acute coronary syndrome (ACS) need urgent transport to a specialist setting [1,2]. In these situations, favourable outcome is inversely related to the time interval between onset of complaints and vascular rescue treatment. However, in daily practice, most patients experiencing chest complaints primarily apply to a general practitioner (GP). Within this population, benign conditions such as thoracic wall complaints, gastric disease or psychiatric and somatoform disease, largely outnumber cases of ACS [3-5]. In specialised care facilities such as coronary care units, 50% of patients presenting with chest pain are diagnosed with ACS, whereas in primary care, ACS is diagnosed in no more than 1.5-22% of cases [6-8]. Referring every patient with chest complaints would overwhelm secondary care facilities, however the GP is faced with serious diagnostic dilemmas since milder diseases with beneficial outcome can mimic ACS and vice versa [9]. Safe exclusion, rather than inclusion, is the main task of a GP in assessing chest complaints.

In primary care, where clearly circumscribed diseases with specific symptoms are embedded in a broad scope of illness and mild disease with less typical appearance, discriminative signs are usually scarce. This applies in particular to ACS, where history, physical examination and electrocardiography notoriously lack sensitivity and specificity as has been extensively surveyed [10-12]. With regard to chest pain, only few signs and symptoms, for example, the absence of pain on chest palpation or presence of pain on exertion, generate discriminative strength in diagnostic studies, although to a limited extent [9,13,14]. Altogether, clinical signs and symptoms are inappropriate for ruling out ACS or lack additive value above the clinical judgment by the GP, which on itself is correct in a majority of cases [6]. Weighing more abstract factors (e.g. contextual patient factors and altered presentation in time) probably leads to this fairly adequate clinical judgment of GPs [15-17].

Because of these diagnostic problems in primary care, most patients presenting complaints possibly matching ACS are still referred to a cardiologist [18]. A low threshold for referring patients with chest complaints to secondary care is an effective strategy for the GP to avert missed cases of ACS [19]. In the Netherlands, this strategy results in 78% of referred patients that are ACS negative in the emergency room (positive predictive value (PPV) is 22%), whereas ACS is present in 5% of patients that are not referred (negative predictive value (NPV) is 95%) and the outcome is probably not severely affected by initially not referring (specificity and sensitivity of clinical assessment by GP: 55%, resp 81%) [6,20]. To enhance triage by a GP and reduce patient burden in secondary care, new diagnostic tools should become available [21]. Combined with signs and symptoms, such tools should be able to safely rule out ACS in a significant number of otherwise referred patients, without a rise in missed cases of ACS. Importantly, this would lead to a significant cost reduction. The number of referred patients would decrease and in the remaining patients who are referred, ACS could be confirmed or ruled out as common in secondary care.

In the field of pulmonary embolism and respiratory tract infections, diagnostic tools combining clinical signs and symptoms with the result of a point of care (PoC) test have recently been introduced. Both increased efficiency by either reducing unnecessary referral (in cases of suspected pulmonary embolism) or treatment (in respiratory tract infections) [22-24]. For ACS, a similar procedure has not yet been defined.

### Biomarkers and point of care testing in primary care

Cardiac troponin T or I (cTnT or cTnI) measurement has become the cornerstone of diagnosing acute myocardial infarction (AMI) [25-29]. Some promising novel biomarkers have featured in recent literature, for example, copeptin and heart-type fatty acid-binding protein (H-FABP) [30-32]. Adding measurements of these markers to troponin in an early phase in emergency room settings increases sensitivity for ACS, but so far the combination has failed to safely rule out ACS in an early stage [33,34]. Until recently, troponin assays have gained sensitivity due to usage of highly sensitive techniques, referred to as high sensitive cardiac troponin (hs-cTn). The additional value of H-FABP testing besides hs-cTn is unclear [35,36]. At this moment, studies reviewing early PoC markers are characterised by methodological imperfections [37]. The function of H-FABP and other early markers combined with signs and symptoms in risk classification in a low prevalence setting such as primary care is still to be determined [38-40].

An earlier study in primary care evaluating a PoC-test on H-FABP did not lead to implementation of PoC-testing in daily practice because of a lack of NPV [20]. However, the PoC device for H-FABP used in this study used a cut-off value of 7 ng/ml, which is above the 99^th^ percentile of 5.7 ng/ml as found in a normal reference population [41]. Retrospective measurement of plasma H-FABP values revealed added value of H-FABP, although insufficient to reach a NPV of 98% or more. Recently, a potential gain in sensitivity for PoC-testing has been found by lowering the cut-off value to 4 ng/ml in a secondary care population, where 50% of patients were diagnosed with AMI [8]. Setting the cut-off value at 4 ng/ml leads to a diagnostic performance equalling that of hs-cTn. Calculated NPV in a primary care population (with an incidence of ACS of 20% or less) would reach 88.3% in patients with a duration of complaints of less than 3 hours and 97.9% in patients with a duration of complaints of 3–24 hours.

When H-FABP-testing is combined with signs and symptoms in a *diagnostic algorithm*, NPV hypothetically improves and thus the number of patients that are referred by a GP but turn out to have no ACS, could be reduced. Even with a moderate amount of false positive results, such an algorithm could improve daily practice since currently, the majority of patients without underlying ACS are referred to secondary care facilities. Thus, our hypothesis is that net reduction of referral rate – without an increase in missed cases of ACS – in patients presenting chest complaints to their GP could be accomplished by the aforementioned algorithm including PoC H-FABP-testing. Therefore a PoC H-FABP-device meeting the demand of a lower cut-off value of 4 ng/ml has recently been developed by FABPulous B.V. We intend to study the diagnostic value of this device in primary care. The methodology of the study is presented in the remainder of this article in order to inform colleagues in the same research field, to anticipate forthcoming results of our study and to prevent publication bias or violation of the protocol during the running time of the study.

### Study design and objectives

This current study is a derivation study to identify signs and symptoms that, combined with point of care heart-type fatty acid-binding protein (PoC H-FABP) testing, can be part of an algorithm to confirm or rule out ACS (meaning AMI and unstable angina (UA)) and AMI alone in a population of patients with complaints possibly due to myocardial ischaemia in general practice. Thus, stage 2 of the 6 major stages in the development and testing of a clinical decision rule as defined by Stiell and Wells will be studied [42]. The diagnostic value of the algorithm will be studied and compared to regular assessment by a GP without PoC H-FABP testing using a delayed type cross-sectional diagnostic model. Both ACS and AMI as a subgroup of ACS will be analysed as final diagnosis. The cost-effectiveness of the test will also be evaluated. The study commenced in November 2013 and will run for two years. External validation of the algorithm derived from this study needs to be performed in future studies.

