### Data collection

Eligible patients will be evaluated by the GP using the following work up schedule:The GP asks written informed consent using a short version of the consent document in the Netherlands or oral informed consent in Belgium.The GP uses the standardised case report form (CRF-HA) for documentation of history and physical examination. If available and if considered as indicated by the GP, an electrocardiogram (ECG) is performed and documented by the GP.The GP is instructed to fill out the presumptive diagnosis together with the decision whether or not to refer to a cardiologist, *before* performing the H-FABP test.The GP obtains one drop of blood from the patient’s finger and starts the PoC H-FABP test. While the test is running, the GP replaces the test in its cardboard package.At this moment, the GP should wait for no less and no longer than 5 minutes before taking the device out of the package again and reading the result. If the GP is still working on point 1–3 as mentioned above in the 5 minutes waiting time, he cannot be influenced by discolouration of the test.Five minutes after starting the test the result is read. The result has to be added to the CRF-HA directly.

By filling out the presumptive diagnosis together with the decision whether or not to refer to a cardiologist on the CRF-HA before reading the result of the PoC H-FABP-test, the regular decision by the GP whether or not to refer to a cardiologist, which is not influenced by the test result, will be formally recorded. Thus, we will be able to compare this regular care with an algorithm using standardised signs and symptoms with PoC H-FABP-testing. This procedure is seen as the next-best option after complete blinding participating GPs for the test result, which is impossible to realise as test results must be read at the point of care within 5 minutes.

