### Primary and secondary outcome

The most important feature of the algorithm of signs and symptoms combined with PoC H-FABP testing will be to adequately categorise all patients as either positive or negative for ACS. The ability of the algorithm to rule in UA in the ACS group is important, since UA is a condition that does not give a rise in biomarkers and diagnosis depends exclusively on signs and symptoms.

Primary outcome: using multivariate analysis of our data, signs and symptoms that have diagnostic value in an algorithm to predict or exclude ACS and AMI will be identified. The primary outcome measures of the study will be *s*ensitivity, specificity, positive and negative predictive value of an algorithm of those relevant signs and symptoms combined with PoC H-FABP testing for ACS and AMI, in patients with thoracic complaints of new onset in general practice. To determine influence of sex, age, duration of the complaints, and kidney function on clinical performance of H-FABP-testing, subgroup analyses within our study population will be performed [47,48].

Secondary outcome: an economic evaluation by means of an incremental cost-effectiveness ratio (ICER) will be performed. This evaluation will be performed by determination of the ratio between the difference in medical costs and the difference in benefits between the two strategies that are observed in this study, being the usual reference policy of the GP and the reference policy that could be created using a determined algorithm consisting of a clinical score and PoC H-FABP-testing. The benefits will be described as reduction in number of referred patients versus missed diagnoses if the algorithm is used.

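### The strategy comparisons and the ICER set a clinical score plus H-FABP against the unaided GP, so a gain cannot be attributed to the H-FABP test, although aims are stated for it

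*Protocol article*

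**What the plan says.** Two statements in the protocol article concern the test itself. The Background section on biomarkers and point-of-care testing ends with "We intend to study the diagnostic value of this device in primary care". Study design and objectives adds "The cost-effectiveness of the test will also be evaluated".

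The stated comparisons concern the combination:

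- Study design and objectives: the algorithm's diagnostic value is to be "compared to regular assessment by a GP without PoC H-FABP testing".
- Data collection: the GP's referral decision is recorded before the result is read, in order to "compare this regular care with an algorithm using standardised signs and symptoms with PoC H-FABP-testing".
- Primary and secondary outcome: accuracy is defined for signs and symptoms combined with H-FABP. The ICER compares two strategies, the GP's usual policy and "the reference policy that could be created using a determined algorithm consisting of a clinical score and PoC H-FABP-testing".
- Sample size and power calculation: the combined algorithm's PPV and NPV are set against those of clinical judgment alone.

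Neither a signs-and-symptoms rule without H-FABP nor GP judgment plus H-FABP is named as a comparator. Two other analyses touch on the test. Primary and secondary outcome plans subgroup analyses of H-FABP performance by sex, age, symptom duration and kidney function. Statistical analyses plans 2 × 2 tables, CART or logistic regression or both, and C-statistics for the models.

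**The concern.** Moving from the GP's unaided decision to the algorithm changes two things: a formal score replaces the GP's overall judgment, and a test result is added. If the algorithm does better, either change could be the reason, and the stated comparison does not separate them.

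The ICER shows this most clearly. The objective is the cost-effectiveness of the test, but a two-strategy ratio gives the cost-effectiveness of score and test together. A score needing no device is not among the strategies. If it delivered most of the gain, the ratio would still credit that gain to a package containing the test.

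The article itself makes attribution uncertain. Primary and secondary outcome says that unstable angina raises no biomarkers and is diagnosed on signs and symptoms alone. For that part of the ACS endpoint, an improvement would have to come from the clinical component.

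**Working it through.** **1. The article's own figure.** Inputs from Sample size and power calculation: N = 600, incidence 22%, sensitivity 85%, specificity 80%.

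- With ACS: 0.22 × 600 = 132. Without ACS: 468.
- True positives 0.85 × 132 ≈ 112, false negatives 20, true negatives 0.80 × 468 ≈ 374, false positives 94.
- PPV = 112/206 = 54.4% (Wald 47.6–61.2%, exact 47.3–61.3%).
- NPV = 374/394 = 94.9% (Wald 92.8–97.1%, exact 92.3–96.9%).

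The stated 54% (47–61%) and 95% (93–97%) are reproduced to within rounding and choice of interval. They describe the combined algorithm only and say nothing about H-FABP's increment.

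**2. The total contrast.** The Daily practice section gives the GP sensitivity 81% and specificity 55%.

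- Change in sensitivity: 85 − 81 = +4 points. Change in specificity: 80 − 55 = +25 points.
- False positives avoided: 0.25 × 468 = 117.
- Referrals per 600 at the planned 22%: GP 0.81 × 132 + 0.45 × 468 = 317.5; algorithm 0.85 × 132 + 0.20 × 468 = 205.8; difference about 112.

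**3. How the specificity gain could divide.** The article gives no accuracy for a score without H-FABP, so score-only specificity *s* is assumed over the whole range from the GP to the algorithm. H-FABP's share is (80 − *s*)/25, and the false positives it removes are 468 × (0.80 − *s*/100).

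| Assumed score-only specificity | H-FABP share | False positives removed by H-FABP |
|---|---|---|
| 55% | 100% | 117 |
| 60% | 80% | 94 |
| 65% | 60% | 70 |
| 70% | 40% | 47 |
| 75% | 20% | 23 |
| 80% | 0% | 0 |

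In every row the algorithm-versus-GP contrast is the same: 80% against 55%.

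**4. Whether the article's H-FABP figures settle the matter.** The section on biomarkers gives a calculated NPV of 88.3% for complaints under 3 hours and 97.9% for 3–24 hours, at an incidence of 20% or less. At exactly 20% (an assumption), LR− = [(1 − NPV)/NPV] / (0.20/0.80).

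- Under 3 hours: (0.117/0.883)/0.25 = 0.53.
- 3–24 hours: (0.021/0.979)/0.25 = 0.086.
- GP: (1 − 0.81)/0.55 = 0.35.

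On these figures the test alone is weaker than the GP early and stronger later. The H-FABP values derive from a secondary-care population in which 50% had AMI; the GP values are for ACS in primary care. The comparison therefore shows only that the contribution has to be measured.

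**5. Whether it can be measured in this study.** Data collection has the clinical findings, the GP's decision and the H-FABP result recorded for each patient, so a with/without comparison is paired. With a true difference of zero and 10–20% discordant classifications (assumed), the 95% half-width is 1.96 × √(discordance/n).

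- Specificity, n = 468: 1.96 × √(0.10/468) = 2.9 points; 1.96 × √(0.20/468) = 4.1 points.
- Sensitivity, n = 132: 1.96 × √(0.10/132) = 5.4 points; 1.96 × √(0.20/132) = 7.6 points.

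**The case against.** A reader might infer that the study cannot show whether H-FABP adds anything. The documents do not support that. The needed data are recorded in each patient and a paired comparison requires no redesign.

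Nor is algorithm versus GP the only planned analysis. The subgroup analyses need the test's own performance, and logistic regression, if used, would estimate an H-FABP effect adjusted for clinical findings. This stands, but it does not fill the gap. Stand-alone accuracy is not added value. Statistical analyses allows CART without regression. An adjusted coefficient shows association, not referrals avoided or ACS missed because of the test.

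It can also be said that the hypothesis, objective and primary outcome concern the algorithm, for which usual care is the right comparator; that this is a derivation study promising no recommendation; and that the list of models belongs in an analysis plan not shown here. The first two are fair, and the comparison with the GP should stay. The third holds for the choice of added-value statistics. It does not hold for the ICER, which the article itself fixes as two strategies while naming the test as the object.

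Finally, Daily practice says that clinical signs and symptoms are unsuitable for ruling out ACS or "lack additive value above the clinical judgment by the GP". That gives little reason to expect the score to explain the whole gain. It is a reason to check, not evidence that the gain belongs to the test.

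**Conclusion.** The concern holds as a mismatch between stated aims and stated comparisons. Aims are given for the device and the test, but the strategy comparisons and the ICER address "a determined algorithm consisting of a clinical score and PoC H-FABP-testing" against the unaided GP. A gain or ratio from them cannot be attributed to H-FABP rather than to the fitted score.

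The size of any misattribution is unknown. H-FABP's share of the 25-point specificity gain can lie anywhere from 0 to 100%. That gain rests on the article's planning values, and the range on assumed score-only specificities.

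The likelihood ratio of 0.53 under 3 hours might tempt a reader to conclude that the test has little rule-out value. The documents do not support that either: the ratio at 3–24 hours is 0.086, eligibility extends to 24 hours, and the H-FABP and GP figures come from different settings.

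**What to change.** In Primary and secondary outcome and in Statistical analyses, prespecify the same clinical model fitted with and without H-FABP in the same patients, using the same candidate variables, fitting procedure and rule for choosing the threshold. Report the paired differences in C-statistic, sensitivity, specificity and NPV, with 95% confidence intervals. Keep the comparison with the GP's recorded decision.

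In the economic evaluation, add the score without H-FABP as a third strategy, so that the step from score to score plus test gives the incremental cost-effectiveness of the test.

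As an optional secondary analysis, compare the GP's pre-test judgment with and without H-FABP.

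The cost is a few more model fits and one more ICER strategy, with no new data. The limitation to state is precision: with 132 ACS cases the sensitivity difference would carry a half-width of about 5 to 8 points under the assumed discordance, so a small effect of H-FABP on missed ACS could not be excluded.

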## Methods

### Recruitment

Two hundred and ten GPs in four regions in the South and Southeast of the Netherlands and the Northeast of Belgium, including both urban and rural areas, will be informed by e-mail of our study and given the opportunity to respond. The first 60 GPs that decide to participate will receive a detailed training in using the test and performing all relevant research activities in order to include ten successive eligible patients, making a total of 600 patients. Inclusion will take place at any time during the day and night, including either during consultation in a primary care facility or during home visits by participating GPs. During evaluations in the study period with participating GP’s, adherence to the protocol and actual recruitment of consecutive cases will be checked and reported.

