### Sample size and power calculation

An incidence of ACS of 22% would generate 132 patients with ACS and 468 patients without ACS in a study population of 600 patients. To create a usable algorithm consisting of signs, symptoms and H-FABP, the sensitivity of this algorithm should reach 85-90% and specificity should reach 80-85%. In a worst case scenario, where sensitivity would be 85% and specificity would be 80%, combined with the incidence of ACS of 22%, PPV of the algorithm of signs, symptoms and H-FABP for ACS would be 54% (95% C.I. 47-61%) and the NPV 95% (95% C.I. 93-97%). These diagnostic values with their 95% C.I. would be of significant interest, since PPV based on clinical judgment only is 22% and NPV is 95%. Therefore, a sample size of 600 generates adequate precision to find clinically relevant improvement of PPV, as compared to the current situation, and NPV that is at least not diminishing.

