### Statistical analyses

Receiver Operating Characteristic (ROC) curves have been used in an earlier stage to find the optimal cut-off point of the venous H-FABP-test [8]. Using 2 × 2 tables and multivariate analyses, including CART analysis, multiple logistic regression, or both, the diagnostic value of the H-FABP-test in combination with clinical findings for ACS and AMI will be assessed [49,50]. Our analysis will result in PPVs and NPVs, sensitivity and specificity and their 95% confidence intervals. Additionally, C-statistics will be presented to quantify overall prediction quality of the models.

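### Ten patients per GP: the PPV and NPV intervals behind the sample size carry no design effect, and the named analyses mention no allowance for clustering by GP

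*Protocol article*

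**What the plan says.** Recruitment describes a two-level sample. It says "The first 60 GPs that decide to participate will receive a detailed training", and each GP is trained "in order to include ten successive eligible patients, making a total of 600 patients". The GPs come from four regions in two countries.

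Sample size and power calculation then works at patient level: "An incidence of ACS of 22% would generate 132 patients with ACS and 468 patients without ACS in a study population of 600 patients". With a sensitivity of 85% and a specificity of 80%, it says the PPV "would be 54% (95% C.I. 47-61%) and the NPV 95% (95% C.I. 93-97". It concludes that "a sample size of 600 generates adequate precision to find clinically relevant improvement of PPV" and an NPV that does not fall. No ICC or design effect appears.

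Statistical analyses names 2 × 2 tables with CART, multiple logistic regression or both. It promises predictive values, "sensitivity and specificity and their 95% confidence intervals". It gives no interval method and does not mention the GP as a unit of sampling.

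**The concern.** Much of what is measured passes through the GP. Under Inclusion and exclusion criteria, the GP judges whether the complaint could be cardiac. Under Data collection, the same GP records history and examination, commits to a referral decision and reads the test strip. The Discussion concedes that inter-observer reliability of the clinical findings is not assessed. Ten patients of one GP may therefore resemble each other more than ten patients of ten GPs.

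If so, 600 patients carry less information than 600 independent ones, and intervals built on independence fall short of 95% coverage. The loss grows with the number of patients per GP in the denominator. It is therefore greatest for the GP's referral rate, the usual-care quantity that the algorithm is meant to improve on, and smallest for sensitivity.

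**Working it through.** **Inputs from the article.** 60 GPs, 10 patients each, N = 600; incidence 22% (132 with ACS, 468 without); sensitivity 85%, specificity 80%. The Background gives a GP sensitivity of 81% and specificity of 55%, used here only for an illustrative referral rate.

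**Assumption.** The ICC is not in the article; 0.02, 0.05 and 0.10 are shown.

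**Step 1: reproduce the stated intervals under independence.**

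- True positives 0.85 × 132 = 112.2; false negatives 19.8; false positives 0.20 × 468 = 93.6; true negatives 374.4.
- PPV = 112.2 / 205.8 = 54.5%. Half-width 1.96 × √(0.545 × 0.455 / 205.8) = 6.8 points, giving 47.7–61.3%. Stated: 54% (47–61%).
- NPV = 374.4 / 394.2 = 95.0%. Half-width 1.96 × √(0.950 × 0.050 / 394.2) = 2.16 points, giving 92.8–97.1%. Stated: 95% (93–97%).

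Wilson, exact and Agresti–Coull versions also agree with the stated limits to within a point. No design effect is needed to obtain the stated figures.

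**Step 2: add the clustering.** Design effect DE = 1 + (m − 1) × ICC, where m is the mean number of patients per GP in the denominator (n / 60). The correct interval is √DE times as wide.

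| Measure | n | m | DE at ICC 0.02 / 0.05 / 0.10 | Interval wider by |
|---|---|---|---|---|
| Sensitivity | 132 | 2.20 | 1.024 / 1.060 / 1.120 | 1.2 / 3.0 / 5.8% |
| PPV | 205.8 | 3.43 | 1.049 / 1.121 / 1.243 | 2.4 / 5.9 / 11.5% |
| NPV | 394.2 | 6.57 | 1.111 / 1.278 / 1.557 | 5.4 / 13.1 / 24.8% |
| Specificity | 468 | 7.80 | 1.136 / 1.340 / 1.680 | 6.6 / 15.8 / 29.6% |
| GP referral rate | 600 | 10.00 | 1.180 / 1.450 / 1.900 | 8.6 / 20.4 / 37.8% |

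These percentages are the widening needed. The shortfall of the uncorrected interval is smaller: 24.8% wider means about 1 − 1/1.248 = 20% too narrow.

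**Step 3: resulting limits.**

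| Measure | Independent | ICC 0.02 | ICC 0.05 | ICC 0.10 |
|---|---|---|---|---|
| PPV | 47.7–61.3 | 47.6–61.5 | 47.3–61.7 | 46.9–62.1 |
| NPV | 92.8–97.1 | 92.7–97.3 | 92.5–97.4 | 92.3–97.7 |
| Specificity | 76.4–83.6 | 76.1–83.9 | 75.8–84.2 | 75.3–84.7 |
| GP referral rate | 48.9–56.9 | 48.6–57.3 | 48.1–57.7 | 47.4–58.4 |

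The referral rate is set at 0.81 × 0.22 + 0.45 × 0.78 = 52.9%; its relative widening does not depend on that value. For this rate, the effective sample size is 600 / 1.45 = 414 at ICC 0.05 and 600 / 1.90 = 316 at ICC 0.10.

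**Step 4: do the conclusions change?** Even at ICC = 1 the PPV half-width is 6.8 × √3.43 = 12.6 points, so the lower limit is about 42%, well above 22%. The rounded NPV interval of 93–97% does not change until the ICC reaches about 0.06. The NPV lower limit of 92.8% is below the 95% comparator before any clustering is added.

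**The case against.** Three stronger readings are tempting, and the article does not support them.

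- A reader might infer that the planned analysis treats patients as independent. Statistical analyses does not say so. It names methods whose standard forms assume independence and leaves the interval method open. A clustered method may sit in a full protocol or analysis plan that is not shown, so its absence from the article is not an error.
- A reader might infer that intervals for specificity and GP referral are already misstated. None is given; only PPV and NPV have stated intervals. The larger widening figures concern results still to come.
- A reader might infer that clustering undermines the claim that NPV does not fall. That claim already lacks margin under independence, so clustering adds slightly to the weakness but does not create it.

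There are also reasons to expect a modest ICC: GPs share a detailed training, use a standardised form and a fixed reading time, and the final diagnosis comes from an independent panel. One ICC range need not suit both missed ACS among test-negatives and referral habits. The algorithm and the GP decision are assessed in the same patients, so single-proportion design effects do not carry over directly to the paired difference.

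All of this stands and limits the size of the point. It does not remove it: the sample-size section makes a precision claim of its own, and its calculation ignores the sampling scheme set out under Recruitment.

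**Conclusion.** The point holds as a modest improvement. The stated PPV and NPV intervals rest on independence, while the design samples 60 clusters of ten. With any positive within-GP correlation they are too narrow. For an assumed ICC of 0.02 to 0.10, their limits move by at most about 0.6 points for NPV and 0.8 for PPV, so N = 600 is not called into question on this ground. The practical weight lies with the specificity interval and the algorithm-versus-GP comparison, where more of each GP's ten patients enter the denominator.

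The sizes assume equal recruitment per GP, the mean denominator per GP as cluster size, a common ICC across measures, and the article's 22% incidence. Uneven recruitment would raise the design effects somewhat.

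**What to change.** In Statistical analyses, state that the intervals for sensitivity, specificity, PPV and NPV, and the paired differences between algorithm and GP decision, take the GP as the cluster. This can be done by a bootstrap that resamples GPs, or by GEE or robust variance. Use GP-clustered standard errors in the logistic model. If an unseen analysis plan already does this, a one-line reference is enough.

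In Sample size and power calculation, label the present intervals as assuming independent patients and add a version at a stated, assumed ICC. At 0.05 this would be PPV 47.3–61.7% and NPV 92.5–97.4%.

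The cost is a little coding and slightly wider intervals. No extra patients and no change in trial conduct are needed.
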